## Abstract

**Background:**

Traumatic brain injury (TBI) is a main cause of severe prolonged disability of young patients. Hospital acquired pneumonia (HAP) add to the morbidity and mortality of traumatic brain-injured patients. In one study, hydrocortisone for treatment of traumatic-induced corticosteroid insufficiency (CI) in multiple injured patients has prevented HAP, particularly in the sub-group of patients with severe TBI. Fludrocortisone is recommended in severe brain-injured patients suffering from acute subarachnoid hemorrhage. Whether an association of hydrocortisone with fludrocortisone protects from HAP and improves neurological recovery is uncertain. The aim of the current study is to compare corticotherapy to placebo for TBI patients with CI.

**Methods:**

The CORTI-TC (Corticotherapy in traumatic brain-injured patients) trial is a multicenter, randomized, placebo controlled, double-blind, two-arms study. Three hundred and seventy six patients hospitalized in Intensive Care Unit with a severe traumatic brain injury (Glasgow Coma Scale ≤ 8) are randomized in the first 24 hours following trauma to hydrocortisone (200 mg.day^-1 ^for 7 days, 100 mg on days 8-9 and 50 mg on day-10) with fludrocortisone (50 μg for 10 days) or double placebo. The treatment is stopped if patients have an appropriate adrenal response. The primary endpoint is HAP on day-28. The endpoint of the ancillary study is the neurological status on 6 and 12 months.

**Discussion:**

The CORTI-TC trial is the first randomized controlled trial powered to investigate whether hydrocortisone with fludrocortisone in TBI patients with CI prevent HAP and improve long term recovery.

**Trial registration:**

NCT01093261

## Background

Traumatic brain injury (TBI) is a leading cause of prolonged disability in young patients. The rate of hospital acquired pneumonia (HAP) varies from 30 to 50% [1-3]. Post traumatic HAP increases the risk of intracranial hypertension [4], prolongs duration of mechanical ventilation and Intensive Care Unit (ICU) length of stay [5,6] and may increase the rate of death [7]. Prevention of one episode of HAP may save 20,000$ [8].

Critical Illness Related Corticosteroid Insufficiency (CIRCI) reaches up to 50 to 70% of trauma patients [9-11]. CIRCI increases systemic inflammation and vasopressive requirement [9,12]. Hydrocortisone decreases rate of HAP and duration of mechanical ventilation in multiple trauma patients with CIRCI [10]. In a sub-group analysis of the HYPOLYTE trial, hydrocortisone appears particularly efficient in multiple trauma patients with TBI [10]. Fludrocortisone was proposed in association with hydrocortisone for the treatment of CIRCI in septic patients [13] and is recommended in BI patients with spontaneous subarachnoid hemorrhage who experience hyponatremia [14]. No data regarding fludrocortisone use in TBI patients are available to date.

The CORTI-TC study aims to test the effects of prolonged low dose of hydrocortisone together with fludrocortisone for prevention of HAP and long term neurological and psychological recovery in patients with severe TBI.

## Methods and Design

### Objectives and design

The Corticotherapy in traumatic brain-injured patients (CORTI-TC) study is a nationwide multicenter, randomized, double blind, placebo controlled trial. The Institutional Review Board of Tours (France) approved the study protocol. The CORTI-TC is conducted in accordance with the declaration of Helsinki and was registered on March 23 2010 at http://clinicaltrial.gov/ with trial registration NCT01093261.

### CONSORT diagram

Figure 1 shows the CONSORT diagram of the CORTI-TC trial.

**Figure 1 F1:**
[figure not shown]
CONSORT diagram of the CORTI-TC trial

### Study population

Investigators screen consecutive severe TBI patients defined as the association of a Coma Glasgow Scale ≤ 8 together with a traumatic anomaly on tomodensitometry. Inclusions criteria are: severe traumatic BI, in the first 24 hours following trauma, age between 15 and 65 years and informed consent from a next-of-kin. Exclusions criteria are: associated tetraplegia, previous immunosuppression, corticotherapy in the previous 6 months, antibiotherapy for active sepsis at the time of inclusion.

### Randomization

Patients eligible for inclusion should be randomized, and the study treatment is started within the first 24 hours. Patients are randomized in a 1:1 ratio in fixed blocks of 12 and stratified according to the center and MGAP score [15] by a computerized number generator list provided by a statistician not involved in the determination of eligibility or in the assessment of outcomes. All assignments are made through a dedicated, pass-word protected, SSL-encrypted website. Randomized patients are given a number corresponding to a «Corti-TC treatment pack» that contains: 20 × 100 mg vial of hydrocortisone or placebo, 10 pills of 50 μg of fludrocortisone or placebo and a sheet for schedule administration.

### Study protocol

Immediately after randomization, and before study drug administration, a short corticotropin test is performed (basal cortisolemia followed by 0.25 mg of synacthene ^® ^and cortisolemia on the 60^th ^min.). Patients are randomized to intravenous infusion of hydrocortisone (200 mg.day^-1 ^for 7 days, 100 mg on days -8 and -9, 50 mg on day-10) with enteral administration of fludrocortisone (50 μg.day^-1 ^for ten days) or to placebo. After receiving the results of the short corticotropin test (usually in the first 48 hours following inclusion), the treatment is stopped if patients have an adapted corticosteroid function.

### Protocol drop-out

Clinicians are allowed to use corticotherapy at any time point if there is an absolute adrenal insufficiency (basal cortisolemia below 30 μg.dl^-1^), a septic shock or an Acute Respiratory Distress Syndrome. Enteral administration of the study drug (Fludrocortisone or Placebo) can be stopped in case of hypernatremia (>155 mmol.l^-1^) associated with a low natriuresis (< 20 mmol.l^-1^). The complete follow up is always performed and patients are kept in the statistical analysis.

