### Statistical consideration

The required sample size is calculated from results of the HYPOLYTE study [10]. The power calculation is performed for comparison between the hydrocortisone and placebo groups in patients with corticosteroid insufficiency. The sample size needed to detect an absolute decrease in pneumonia incidence of 20% is 121 patients in each group, assuming a rate of 70% in the placebo group, in a 2-sided test performed with a statistical power of 90% and an α risk of 5%. Assuming a rate of 75% of corticosteroid insufficiency [10], 326 patients (approximately 163 patients in each group, and 41 patients with normal corticosteroid function who are untreated) are needed. Two a priori interim analyses using the O'Brien and Fleming method for α risk spending are planned respectively after the inclusion of 110 and 220 patients.

An ITT and a mITT analysis will be performed. Because the patients with adapted corticosteroid function are left untreated (when the cosyntropin test show no corticosteroid insufficiency), a modified intention-to-treat (mITT) analysis that includes only the patients with corticosteroid insufficiency is planned.

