Major modifiable risk factors for HAP as described by the American thoracic Society [23] are prospectively collected: oropharyngeal decontamination, proclive (>30°), stomach ulcer prevention, insulinotherapy, tracheostomy and protocol for sedation. All these factors can not be standardized in the protocol. Sedation is a cornerstone therapy for intracranial hypertension [24]. Therefore, it was not practical to perform either daily spontaneous breathing trials or daily liberation from sedation in a population of traumatic brain injury patients. Concerning tracheostomy, prevention of HAP by performing tracheostomy early is still debated. In a recent study, the incidence of HAP was similar in patients with early versus late tracheostomy [25]. None of the participating ICUs usually perform early tracheostomy or "daily spontaneous breathing" in TBI patients during the study period. Regarding insulinotherapy, tight glycemia control is a highly debated topic for ICU patients and is associated either with beneficial [26] or deleterious effects [27]. A tight glycemic control was not associated with any survival improvement of septic patients treated with hydrocortisone [28]. Proclive and oropharyngeal decontamination are commonly used in participating ICUs. Finally, a controlled double-blind randomized design may ensure the comparability of groups for the majority of interventions other than hydrocortisone infusion.

In this study, we use a placebo in a population of CIRCI patients. This point do not raise an ethical issue as the recommendations for the diagnosis and treatment of CIRCI recently published by the American College of Critical Care Medicine [29] state that: first, given the lack of data, treatment of CIRCI is not recommended in other population than septic shock patients; second, a call for studies in ICU populations other than septic patients (including trauma patients) was advocated. Moreover, a placebo is ethically justified because the placebo is given in addition to standard of care of TBI patients.

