The selection of ICU patients who require hydrocortisone treatment is of particular importance. The concept of CIRCI has recently been introduced to differentiate the classical chronic corticosteroid insufficiency (Addison's disease) from the alteration of the hypothalamic-pituitary-adrenal axis observed in ICU patients [29]. CIRCI corresponds to an inadequacy between the severity of illness and the corticosteroid activity [19]. The combination of basal cortisolemia and/or a delta <9 μg/dl provides the best specificity and sensitivity for the diagnosis of CIRCI associated with severe sepsis [30]. Finally, recent recommendations have advocated use of either the basal cortisolemia or delta for diagnosis of CIRCI [31]. Regarding threshold of the basal cortisolemia, our definition is more liberal (<15 μg/dl) than the consensus statement (< 10 μg/dl). In the HYPOLYTE study using this liberal definition [10], patients with a normal corticosteroid function have a trend toward a decrease in rate of HAP as compared to patients with corticosteroid insufficiency treated with placebo (P = .06). Finally, the Corti-TC trial is not designed to test the accuracy of the CIRCI definition in trauma patients.

Despite inhibition of the cortisol synthesis, etomidate is recommended for Rapid Sequence Induction of multiple trauma patients [31]. For single bolus injection, the duration of adrenal blockade varies from 12 hours [32] to 24 hours [33], but it should be noted that this blockade was inconstantly reported [34]. In the Corti-TC study, a corticotropin test will not be performed within the first 8 hours following etomidate infusion and etomidate use in ICU is discouraged. Finally, as etomidate use may impact the results, etomidate will be considered as an effect modifier for the analysis (sensitivity analysis).

In conclusion, the Corti-TC trial is a nationwide investigator-initiated randomized controlled trial powered to test the hypothesis that the association of hydrocortisone with fludrocortisone in severe TBI patients prevents HAP. The Corti-TC trial also determines the effects of low dose of corticosteroids on duration of mechanical ventilation, length of ICU stay, organ failures and rate of death. An ancillary study will assess the long term neurological and psychological recovery of the included patients.

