## Trial status

On October, the 5th of 2011, 110 patients have been enrolled in the study. The first interim analysis will be performed in november 2011, after the collection of the primary end point of the 110th patient.

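### The cortisol trigger for open-label corticosteroids is printed as below 30 μg/dl, twice the trial's own liberal cut-off of 15 μg/dl, and is wrong as written

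*Protocol article*

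**What the plan says.** The Protocol drop-out section lists three situations in which open-label corticosteroids are permitted: absolute adrenal insufficiency, septic shock and acute respiratory distress syndrome (ARDS). For the first it gives a number: "Clinicians are allowed to use corticotherapy at any time point if there is an absolute adrenal insufficiency (basal cortisolemia below 30" μg/dl). Patients treated this way are retained: "The complete follow up is always performed and patients are kept in the statistical analysis".

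The Discussion describes how corticosteroid insufficiency is identified. On the basal value it says "Regarding threshold of the basal cortisolemia, our definition is more liberal (<15" μg/dl), set against a consensus value of 10 μg/dl. On the response to corticotropin it cites work in severe sepsis: "The combination of basal cortisolemia and/or a delta <9" μg/dl.

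Two other parts of the article depend on this classification. Under Study protocol, study drug is stopped once the corticotropin test shows adapted function. Under Statistical consideration, the trial is powered on patients with corticosteroid insufficiency ("Assuming a rate of 75% of corticosteroid insufficiency [10], 326 patients" are needed), and the modified intention-to-treat analysis is restricted to them.

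**The concern.** Absolute insufficiency should be the narrower and more severe state within corticosteroid insufficiency, so its cortisol limit should be lower than the limit for the wider condition. The article prints the reverse.

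This number is a decision rule. It determines which randomised patients may be given the drug class under test outside the randomised comparison. If sites worked from 30 μg/dl, some placebo patients in the population on which the trial is powered could receive open-label corticosteroid. Any such use before pneumonia would narrow the contrast between arms. Recruitment was under way at publication ("110 patients have been enrolled in the study", with the first interim analysis planned for November 2011), so the check had practical value at that point.

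**Working it through.** The disputed figure is a clinical threshold, so there is no formula to reproduce. The check compares the article's cortisol limits and follows the rules through.

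**Inputs**
- Open-label trigger: basal cortisol < 30 μg/dl (Protocol drop-out).
- Trial's basal cut-off for corticosteroid insufficiency: < 15 μg/dl (Discussion).
- Consensus basal cut-off: < 10 μg/dl (Discussion).
- Delta cut-off: < 9 μg/dl (Discussion). It is cited from sepsis work, and I take it to be the trial's delta criterion.
- Study drug stops if function is adapted (Study protocol).

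**Ratios**
- 30 / 15 = 2.0 times the trial's own cut-off.
- 30 / 10 = 3.0 times the consensus cut-off.

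All three limits concern basal cortisol in μg/dl, so a difference in analyte or stated unit does not explain the gap.

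**What the printed rules imply for each type of patient**

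| Basal cortisol (μg/dl) | Delta (μg/dl) | Trial classification | Meets the printed cortisol trigger? |
|---|---|---|---|
| below 15 | any | insufficient | yes, always |
| 15 to below 30 | below 9 | insufficient (delta only) | yes |
| 15 to below 30 | 9 or more | adapted, study drug stopped | yes |
| 30 or more | below 9 | insufficient (delta only) | no |
| 30 or more | 9 or more | adapted, study drug stopped | no |

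**Reading the table**
1. First row: any value below 15 is also below 30. Every patient insufficient on the basal criterion therefore qualifies, in either arm. The trigger does not pick out a more severe subset of them.
2. Third row: the same test result classes a patient as having adapted function, so that study drug stops, and as absolutely insufficient, so that open-label corticosteroid is permitted. The two labels are incompatible.
3. Fourth row: the trigger does not cover everyone with corticosteroid insufficiency. Patients insufficient by delta alone qualify only if their basal value is also below 30.

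The article does not give the distribution of basal cortisol, so the number of patients in each row cannot be calculated. It also gives neither the frequency of open-label use nor its timing relative to pneumonia. I therefore offer no power figure, because any such figure would rest on an invented contamination rate.

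**The case against.** The strongest reply is that this is one number, printed once in a condensed article, and most likely a misprint. If so, conduct was unaffected and only the publication needs correcting. That largely stands, and it limits the severity. It does not remove the point: the number and its unit are intact in the text, nothing elsewhere explains them, and a rule on access to the tested drug class should be right where it is published.

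A second reply is that the rule permits treatment and does not direct it. That also stands. A reader might infer that the rule contradicts the case made for placebo in the Discussion, which reports guidance that "treatment of CIRCI is not recommended in other population than septic shock patients". It does not. A permission sits awkwardly with that guidance, but the guidance also gives clinicians a reason not to use the permission routinely.

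A reader might go further and infer that the placebo arm was contaminated and power lost. The article does not support this. It does not show that any site was given 30 μg/dl, and no passage supports any particular rate of open-label use. Corticosteroid started after pneumonia would not alter the primary endpoint either.

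Finally, it can be said that no corrected number is available. That is true. A dropped decimal and a unit slip are both possible, and the article does not decide between them.

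**Conclusion.** The figure is wrong as written. A limit of 30 μg/dl for absolute insufficiency cannot stand beside the trial's own liberal limit of 15 μg/dl for insufficiency in general. I hold this with high confidence, because it rests only on two statements in the same article about the same measurement.

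The size is minor to moderate. What is established is a factor of two against the trial's cut-off, a trigger that takes in everyone insufficient on the basal criterion, and a contradictory classification for patients at 15 to 30 μg/dl with an adequate delta. The last of these assumes that the trial applies the delta criterion quoted in the Discussion. That the number is a misprint is probable but not shown. Whether the rule affected any patient is unknown.

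**What to change.** - Check the figure against the full protocol and the instructions issued to sites.
- Have the sponsor state the intended value and publish an erratum. The value must be clearly stricter than 15 μg/dl. A limit only just below 15 would satisfy the ordering but still admit nearly everyone insufficient on the basal criterion.
- If sites were given 30 μg/dl, send a clarification or short amendment. If open-label corticosteroid use is recorded, report it by arm. The variables listed under Follow up do not mention it, so availability has to be confirmed first.
- Keep the septic shock and ARDS provisions, and keep these patients in follow-up and in the analysis, as the article already states.

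The cost is an erratum if only the article is wrong. If sites used the figure, it also takes a letter or short amendment and one tabulation, provided the data exist.

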### Biological assessment

Immediately before starting the treatment, but at least 8 hours after a bolus injection of etomidate [10,13], a short corticotropin test is performed: cortisolemia before and 60 minutes after an intravenous bolus of 0.25 mg of corticotropin (Novartis ^®^, Rueil-Malmaison, France). A second short corticotropin test is performed on day-11 or -12. At the same time points, plasma and serum are frozen at -80°C for ancillary studies.

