### Statistical analysis

Primary outcome is the occurrence of HAP within the first 28 days after randomization. The primary analysis will use a Cox multivariate proportional hazards model that includes 2 predefined covariable: MGAP [15] and Coma Glasgow Score. We will also perform complementary sensitivity analyses with an adjustement on etomidate use. Corresponding hazard ratios (HRs) along with their 95% confidence intervals (CIs) will be reported. The crude percentages and the Kaplan-Meier estimators will also be presented. Cumulative incidence will also be estimated for the primary outcome by treating deaths as competing risks. The Fine and Gray model [16] will be used. If a difference is confirmed for the primary endpoint, sub-group analysis for multiple trauma (presence or absence), hyporeactivity to adrenocorticotrophic hormone (presence or absence), early treatment administration (<18 hours after trauma or >18 hours) will be performed. In order to control the family wise error rate, a stepwise hierarchal testing procedure will be used for subgroup analyses.

Normally distributed variables will be expressed as mean and standard deviation; non-normally distributed variables will be expressed as median and inter quartile ranges. Categorical variables will be expressed as numbers and percentage, as well as the absolute difference (95% CI). Linear or logistic regressions will be used as appropriate for the secondary endpoints.

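### The corticotropin test is allowed from 8 hours after etomidate although the article puts the blockade at 12 to 24 hours, and the planned adjustment for etomidate use cannot show whether the mITT result depends on the patients affected

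*Protocol article*

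**What the plan says.** The Biological assessment section places the first corticotropin test "Immediately before starting the treatment, but at least 8 hours after a bolus injection of etomidate". The Discussion repeats the rule: "a corticotropin test will not be performed within the first 8 hours following etomidate infusion and etomidate use in ICU is discouraged". The same paragraph states: "For single bolus injection, the duration of adrenal blockade varies from 12 hours [32] to 24 hours [33", and adds that "it should be noted that this blockade was inconstantly reported".

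Two other sections bear on the timing. Study protocol says: "Immediately after randomization, and before study drug administration, a short corticotropin test is performed", with no exception for etomidate. Randomization says that "the study treatment is started within the first 24 hours".

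The test result has two uses. Study treatment is stopped in patients whose adrenal function is adequate (Study protocol), and only patients found insufficient enter the mITT analysis (Statistical consideration). The power calculation is made for patients with insufficiency. An ITT analysis is planned as well.

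On etomidate, the Statistical analysis section says: "We will also perform complementary sensitivity analyses with an adjustement on etomidate use". The Discussion instead announces that etomidate will be handled as an effect modifier, within a sensitivity analysis. The Follow up section lists etomidate use among the variables collected.

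**The concern.** The permitted wait is shorter than both blockade durations that the article cites. A patient whose adrenal axis would otherwise respond normally can be tested while the drug still suppresses it, be classed as insufficient, stay on study drug and be counted in the mITT set. If such patients gain less from treatment, the mITT effect is pulled towards zero in the population for which the trial was powered.

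The two descriptions of the etomidate analysis do not match. Adjusting for etomidate use estimates one common treatment effect, conditional on etomidate. It does not ask whether the effect differs between exposed and unexposed patients, and it leaves in the set everyone tested inside the blockade. As specified, the analysis cannot deliver what the Discussion promises.

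**Working it through.** **1. Timing, from the article's own figures.** Minimum wait: 8 h (Biological assessment; Discussion). Blockade: 12 to 24 h (Discussion).

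- Shortfall against the lower figure: 12 − 8 = 4 h.
- Shortfall against the upper figure: 24 − 8 = 16 h.

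If etomidate is given after the trauma and the 24-hour limit for starting treatment runs from the trauma, a test done on schedule comes at most 24 h after the bolus. By the upper figure every such test lies inside the blockade. By the lower figure only tests between 8 and 12 h do.

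**2. When the timing statements collide.** Testing straight after randomisation and waiting at least 8 h after etomidate conflict only for a patient randomised less than 8 h after the bolus. The 8 h wait and the 24 h limit conflict only if etomidate is given later than 24 − 8 = 16 h after trauma. Otherwise all three can be met.

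**3. The plan's sample size.** Inputs from Statistical consideration: 70% on placebo, a 20-point reduction (so 50% on treatment), two-sided 5%, power 90%, 75% insufficient.

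- n per group = (1.960 + 1.282)² × (0.70×0.30 + 0.50×0.50) / 0.20² = 10.507 × 0.46 / 0.04 = 120.8, so 121, as stated.
- Total = 242 / 0.75 = 322.7, so 323, against the stated 326 (within 3%).

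No stated figure is put in doubt here. With the pooled-variance formula, 121 per group gives power 0.893, and 124 per group are needed for 90%.

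**4. Illustration of dilution.** Let f be the share of the mITT set suppressed only by etomidate. The documents do not give f. Assume no treatment effect in that share and a pneumonia rate r there of 70% or 50%. Then:

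- placebo rate = (1 − f)×0.70 + f×r
- treated rate = (1 − f)×0.50 + f×r
- difference = (1 − f)×0.20

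| f | Rates, r = 70% | Power, 121 per group | Rates, r = 50% | Power, 121 per group | n per group for 90% |
|---|---|---|---|---|---|
| 0 | 70 v 50 | 0.893 | 70 v 50 | 0.893 | 124 |
| 5% | 70 v 51 | 0.861 | 69 v 50 | 0.858 | 138–139 |
| 10% | 70 v 52 | 0.823 | 68 v 50 | 0.816 | 153–155 |
| 20% | 70 v 54 | 0.730 | 66 v 50 | 0.715 | 192–198 |
| 30% | 70 v 56 | 0.617 | 64 v 50 | 0.596 | 248–261 |

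**5. Why f cannot be filled in.** It would need the proportion given etomidate, the distribution of the etomidate-to-test interval, how often the blockade actually occurs, and how many of those patients would have been insufficient anyway. The article gives none of the first three. Its general insufficiency rates (50 to 70% in the Background, 75% in Statistical consideration) suggest that many would have been.

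**The case against.** The article does not hide the issue. It notes that the blockade is inconstant, discourages etomidate in ICU, records its use and plans a sensitivity analysis. A reader might infer that covariate adjustment is the only remedy planned. That is not so, because the Discussion names effect modification. What remains is that the section that specifies the analysis does not carry this out.

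A reader might also infer that the timing rules cannot be followed. The 8-hour rule reads naturally as a qualification of the general instruction, and the conflict is limited to the cases worked out above. The Discussion presents etomidate as a drug for rapid sequence induction, so nothing suggests that late boluses are common. Nor does this conflict cause the possible misclassification, which follows from 8 hours against 12 to 24 hours alone.

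It can be argued that the mITT population is simply those insufficient on the trial's test, whatever the cause. The article describes insufficiency functionally and says that the trial is not designed to assess the accuracy of the definition. This stands against any claim that the mITT set has lost its target population. It does not remove the question whether the effect is the same in patients suppressed only by the drug.

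Finally, the trial cited for the sample size is also cited at the 8-hour rule. If it used the same wait, its rates may already include such patients, and there might be no loss relative to plan. This cannot be checked from the article, and it is a good reason to treat the power figures as illustration only.

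**Conclusion.** The point holds in limited form. The minimum wait is 4 to 16 hours shorter than the blockade durations cited, so the mITT set may include patients suppressed only by etomidate, and the specified adjustment neither tests effect modification nor examines those patients.

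A stronger reading, that the randomised comparison is biased or type I error inflated, is not supported. The test precedes study drug in both blinded arms, so selection should be balanced, and the ITT analysis is not selected on the test. The possible harm is dilution, and only if these patients benefit less. Under the assumption that they gain nothing, power falls from 0.89 to about 0.82 at a 10% share and to about 0.72 at 20%. Those shares are assumed, and the documents do not allow the true one to be estimated. Which timing is clinically right is not judged here.

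**What to change.** In the Statistical analysis section, replace the adjustment-only sensitivity analysis with a treatment-by-etomidate interaction in the Cox model, so that it matches the Discussion. Report the treatment effect with its confidence interval in exposed and unexposed patients, since an interaction test alone will have little power.

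Record the interval from etomidate injection to corticotropin test. Repeat the mITT analysis without patients tested within 12 hours of etomidate, and again without those tested within 24 hours. These are the article's own two figures. The interval is fixed before study drug is given, so the restricted comparisons remain between randomised arms. If tests are done on schedule, the 24-hour run will come close to an analysis of patients who received no etomidate after trauma, and should be described as such.

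The cost is one recorded time, one model term and two further runs. The downside is wider intervals in the restricted sets, which also lose some patients who are truly insufficient.

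Separately, the investigators should reconcile the timing statements in Randomization, Study protocol and Biological assessment for patients randomised less than 8 hours after etomidate or given it late in the 24-hour window.
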